### Ethics Approval

Ethics approval was received from Human Research Ethics Committees of St Vincent's Hospital, The Austin Hospital, The Royal Melbourne Hospital, The Geelong Hospital, The Prince Charles Hospital, The Royal Brisbane and Women's Hospital, and Monash University.

### Study conditions

Both control and intervention participants receive a brief National Heart Foundation of Australia education pamphlet on MI recovery and a biennial study newsletter based on existing educational materials to enhance study retention. On enrolment, a letter is sent to all participants' primary care provider/s informing them of the aims of the study, the group to which the patient has been randomised and other relevant information that may be required from the participant and the care provider at follow-up.

#### Control

Control participants continue to receive their usual medical care through their health care providers.

#### Intervention

The intervention commences within two weeks of baseline screening and is delivered by qualified psychologists ('counsellors') from Monash University. The intervention aims to manage depression as well as CHD risk factor behaviours using a tele-based care management model [30] incorporating CBT counselling [31]. Two psychologists with at least 2 years of relevant clinical experience with CBT are delivering the intervention. The counsellors provide information to patients via the telephone during structured counselling sessions and assist participants to set and attain specific short and long term goals and a plan of action to improve their mental health and CHD risk factor profiles. Cognitive restructuring, behavioural activation, goal setting and motivational interviewing techniques are utilised. Participants are encouraged to seek appropriate treatment and attend follow-up with their usual health care providers as necessary, in addition to activating social/family support and community and environmental linkages (e.g. employment, housing support). The intervention comprises up to 10 × 30-40 minute sessions over a six month period as CBT has been found to effectively reduce depressive symptoms over this time frame [22]. The sessions are most intensive over the first three months when depressive symptoms are most likely to affect patients following ACS [32] and to impact on their HRQOL and adoption of positive CHD risk factor behaviours. More frequent sessions may be scheduled during the treatment phase based on a patient's needs and interest but the intervention is limited to up to 10 sessions in total.

Intervention participants receive a handbook containing both project specific and general health resources. For example, the handbook contains monitoring forms and recording sheets to be used during and in between sessions for tracking the participant's mood, session activities, the participant's thoughts, CHD risk factor goals and changes. It provides additional information and details on the nature and treatment of depression, as well as the CBT model. More generally, supplementary materials including a list of health related resources are provided in the handbook.

### Study Integrity

The study design is guided by the CONSORT statement [33] and randomisation to study group occurs following the completion of Time 1 data collection. Project staff who are collecting data are blinded to participants' group allocation. Participants are asked not to reveal the group to which they have been randomised when completing data assessments. Stratified randomisation occurs using a separate block randomisation list that has been generated for each study group or strata. Randomisation is integrated into the web-based database and automatically generated following the conclusion of baseline assessment. The process is concealed from investigators. The schedule is stratified by severity of depression assessed by the CIDI (i.e. those meeting current diagnosis for depression versus those who do not). The intervention protocol is detailed in a manual. In addition to internal peer review, all intervention calls are audio-taped with a proportion reviewed by a senior clinical psychiatric consultant, using a standardised inventory in order to ensure clinicians' adherence to the delivery of the intervention protocol and treatment integrity. To assess the quality of the delivery of the intervention, a separate inventory based on the Cognitive Therapy Scale [34] has been developed for the MoodCare intervention. All data analyses are conducted on the basis of intention to treat.

### Data collection and outcome measures

Clinical and anthropometric data are collected at the time of the participant's initial screening, from hospital medical records (blood pressure, cholesterol level, haemoglobin A1C (HbA1c), family history of heart disease, height, weight, waist circumference, body mass index (BMI), procedures performed or scheduled, General Practitioner (GP) details, cardiologist details, whether patient was transferred from another hospital, details of initial admitting hospital, admission and expected discharge date). At follow-up, participants are requested to collect medical information (blood pressure, cholesterol level, HbA1c, weight, waist circumference) from their primary care provider/s medical records prior to Computer Assisted Telephone Interview (CATI). Self-report and CIDI interview data are collected, at Time 1, Time 2, Time 3 and Time 4 by CATI. Additional outcome data are collected via postal survey to minimise participant burden (see Table 1). The feasibility of the trial will be determined by the following outcome measures:

**Table 1 T1:** Measurement of outcome variables at baseline (Time 1), post-intervention (Time 2), 12 months (Time 3), 24 months follow-up (Time 4)

Variable	Measurement tool	Inpatient Screening	1-2 weeks post discharge TIME 1	6 Months TIME 2	12 Months TIME 3	24 months TIME 4	Type of administration
**Depression**	Patient Health Questionnaire 9	✓	✓	✓	✓	✓	CATI^+^

	Two item screener [28]		✓				CATI

	Cardiac Depression Scale		✓	✓	✓	✓	CATI

	Composite International Diagnostic Interview		✓		✓	✓	CATI

**HRQOL**	Short Form 12		✓	✓	✓	✓	CATI

**Physical activity**	Active Australia Survey		✓	✓	✓	✓	Postal survey*

**Saturated Fat Intake**	Short Fat questionnaire		✓	✓	✓	✓	Postal survey*

**Social Support**	ENRICHD Social Support Inventory		✓	✓	✓	✓	CATI

**Smoking**	Cancer Council Food Frequency Questionnaire		✓	✓	✓	✓	Postal survey*

**Alcohol**	Cancer Council Food Frequency Questionnaire		✓	✓	✓	✓	Postal survey*

**Medication**	Self report/General Practitioner/data linkage		✓	✓	✓	✓	Postal survey,* medical records

**Anxiety**	General Anxiety Disorder-7		✓	✓	✓	✓	CATI

**Medical co-morbidities**			✓	✓	✓	✓	CATI

**Biomedical and anthropometric measurements**	Weight, height, waist circumference, Blood Pressure, lipids, fasting capillary blood glucose	✓			✓	✓	Medical records

**Employment**	Employment status, absenteeism/productivity		✓	✓	✓	✓	CATI

CATI = Computer Assisted Telephone Interview; *An envelope containing self administered paper copies of each instrument is posted to the participant prior to their baseline telephone interview. The survey is to be completed on approximately the same day as baseline CATI interview to ensure consistency of information, and returned to the Project Manager. ^+ ^In patient screening conducted face to face by nurses, using the PHQ9. Follow up PHQ9 administered via CATI at all assessment points thereafter

#### Changes in key depression and HRQOL outcomes

The two primary outcomes are changes in depression and HRQOL which are assessed using the CDS [35] and SF-12 [36], respectively. The CDS was originally designed to measure depressed mood over the full range generally seen in cardiac patients, combining excellent test-retest reproducibility with responsiveness to change over time [29]. In addition, it also has excellent sensitivity (97%) and appropriate specificity (85%) for the categorical diagnosis of major depression [37]. Other outcome variables include: physical activity [38], saturated fat intake [39], smoking, alcohol intake [40], anxiety [41], social support, employment, lipid profile, blood pressure, BMI, waist circumference, diabetes management (HbA1c), and pharmacological management (self report, health care utilisation data). Six month follow up will be the primary assessment point. The measures for each of these outcome variables are summarised in Table 1.

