#### Sample Size Calculations

Anticipating an attrition rate of 20% throughout the study, n = 125 participants are required to achieve a final sample size of n = 100. Sample size analysis indicated that 50 subjects per group (intervention and control) or a total of 100 are required to complete the study in order to detect an absolute intervention effect with 80% power and type I error of 5% (two-tailed). Sample size was calculated based on an overall difference between participants in the intervention and control groups in the primary outcome measure of depression scores at 6 months, where a sample size of n = 100 was sufficient to detect a difference in mean CDS scores of 6.8, assuming a between-patient SD of 12 [29]. Assuming persistence of effect to 12 months and a conservative correlation of 0.30 between baseline, 6 months and 12 months CDS scores, a pooled analysis at 6 and 12 months will have 80% power to detect a difference of 5.1 units (a change score of 5 on the CDS is considered clinically meaningful).

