### Data Analyses

Baseline characteristics will be compared across intervention arms using summary statistics. Principal analyses will involve comparison of CDS and HRQOL outcomes at each time point between intervention arms using the baseline of the outcome as a covariate where relevant. Pooled analyses across all time points will employ linear mixed models. This will assess comparative rates of change over time, variability between rates of individuals, and allows for incomplete data due to a process of missingness where systematic dependence is upon observed covariates or outcomes, the so called "missing at random" assumption. Results will be expressed as estimated mean changes in CDS depression measures and HRQOL, as an overall mean excess intervention over usual care effect, all with corresponding 95% confidence intervals.

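### The sample size section has one primary outcome and the outcomes section has two, so the stated 5% error and 80% power cover the CDS only

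*Protocol article*

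**What the plan says.** Three sections of the protocol article bear on which outcome decides the trial.

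- **Sample Size Calculations.** The trial is sized on a difference between groups "in the primary outcome measure of depression scores at 6 months". It is meant to "detect a difference in mean CDS scores of 6.8, assuming a between-patient SD of 12", with 80% power and a two-tailed 5% error. A second power statement, for 6 and 12 months pooled, is also in CDS units. No effect size, SD or power is given for the SF-12.
- **Changes in key depression and HRQOL outcomes.** Here the article names a pair: "The two primary outcomes are changes in depression and HRQOL which are assessed using the CDS [35] and SF-12 [36], respectively". The same paragraph makes 6 months the primary assessment point.
- **Data Analyses.** "Principal analyses will involve comparison of CDS and HRQOL outcomes at each time point between intervention arms". Results for both outcomes are to be reported with 95% confidence intervals.

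The Primary Aim lists both outcomes, next to cost-effectiveness and acceptability. The hypothesis that closes the Background joins depression and HRQOL at 6 months with the word *and*, but sets no formal success rule.

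**The concern.** The number of primary outcomes is given twice and differently. The 5% and the 80% were derived for the CDS and not extended to the second primary outcome named later. A reader cannot tell which result decides the trial. With a null CDS and a positive SF-12, the outcomes section supports reporting a primary success and the sample size section supports reporting a primary failure. That choice has to be closed before the data are seen. Depending on how it is closed, either the error rate or the power in the sample size section may no longer describe the trial.

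**Working it through.** **Inputs from Sample Size Calculations:** CDS difference 6.8, SD 12, two-sided alpha 0.05, power 0.80, 50 completers per group, attrition 20%. **Not in the document, so assumed:** the correlation r between the CDS and SF-12 test statistics (both oriented so that positive means benefit), and the power for the SF-12.

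**1. Reproduce the plan's figures.**
- n per group = 2 × (1.960 + 0.842)² × 12² / 6.8² = 48.9, so 49 (stated 50).
- Standard error at 50 per group = 12 × √(2/50) = 2.4. Power = Φ(6.8/2.4 − 1.960) = Φ(0.873) = 80.9% (80.1% with the t distribution).
- Detectable difference = 2.802 × 2.4 = 6.72 (6.79 with t; stated 6.8).
- Enrolment = 100 / (1 − 0.20) = 125, as stated.

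The calculation is sound, and it uses the full 5% on one CDS comparison.

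**2. One primary outcome, CDS.** The 5% and 80% hold. The outcomes section is then wrong to name two.

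**3. Two primaries, either one suffices, each at two-sided 5%.** Chance of at least one false positive at 6 months = 1 − P(|Z₁| ≤ 1.96 and |Z₂| ≤ 1.96). For r = 0 this is 1 − 0.95² = 9.75%. The bivariate normal gives the rest:

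| r | 0 | 0.3 | 0.5 | 0.7 | 0.9 |
|---|---|---|---|---|---|
| At least one false positive | 9.75% | 9.5% | 9.1% | 8.3% | 7.0% |

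Splitting alpha as 0.025 each:
- CDS power at 50 per group = Φ(2.833 − 2.241) = 72.3%.
- Detectable difference = (2.241 + 0.842) × 2.4 = 7.4.
- To keep 80% power: 2 × (2.241 + 0.842)² × 144 / 46.24 = 59.2, so 60 per group, and 120 / 0.80 = 150 enrolled.

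**4. Two primaries, both required, each at two-sided 5%.** The error does not exceed 5%. Joint power = P(Z₁ > 1.96 and Z₂ > 1.96), each Z with mean 2.80 (80% power on each outcome):

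| r | 0 | 0.3 | 0.5 | 0.7 |
|---|---|---|---|---|
| Joint power | 64.0% | 66.6% | 68.7% | 71.3% |

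At r = 0 this is 0.80². Giving the SF-12 the same standardised effect as the CDS at 50 per group (mean 2.83) changes the range only to 65.4% to 72.4%.

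**5. Fixed sequence, CDS then one SF-12 score, each at two-sided 5%.** If there is no CDS effect, any false claim must begin with a false CDS rejection, which has a 5% chance. If the CDS effect is real and the SF-12 effect is not, a false claim needs an SF-12 rejection, at most 5%. Overall error is at most 5%, and CDS power remains that of step 1.

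**The case against.** A reader might infer that the trial tests both outcomes at 5% and that the stated 5% error therefore fails. The document does not support this as a fact. It attaches 5% to the CDS calculation only; a 5% test of the SF-12 is inferred from the 95% intervals. The 5% is right for the CDS alone, and right again if both outcomes must succeed, which the conjunctive wording of the hypothesis allows. Inflation arises only if one success suffices, and no section says so.

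A reader might also count every visit, or two SF-12 summary scores, as further primary tests. The outcomes section makes 6 months the primary assessment point and the later visits belong to a secondary aim, so the visits do not multiply the primary tests. The article does not say how many SF-12 scores would be tested, so an error rate for three tests is conjecture.

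It can further be said that the sample size section never calls the CDS the only primary outcome, that sizing on one of a pair makes no stated figure wrong, that this is a feasibility trial, and that an alpha split or testing order may sit in an analysis plan not shown. The last point stands: the absence of a multiplicity procedure is not the finding. The others narrow the point but do not remove it. The article itself speaks of a primary outcome measure in the singular and then of two, and an analysis plan would inherit that conflict. The feasibility label does not settle it either, since the article sets a formal power calculation and its Discussion says that efficacy will be evaluated.

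**Conclusion.** The sample size section and the outcomes section disagree on the number of primary outcomes, and the stated 5% and 80% apply to the CDS at 6 months only. The consequence depends on a rule that the article does not give:

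- either suffices, unadjusted: about 7% to 9.75% chance of a false-positive primary result at 6 months (assumed correlation 0.9 to 0);
- both required: 5% holds, but the power for trial success is about 64% to 71% (correlation 0 to 0.7, assuming 80% power for the SF-12, for which the article gives no figure);
- CDS alone: both stated figures hold, and the naming of two primaries does not.

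The contradiction needs no assumption. The sizes rest on the assumed correlation and, for joint power, on the assumed SF-12 power.

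**What to change.** Reconcile Sample Size Calculations, the outcomes section and Data Analyses with one rule: test the CDS at 6 months first at two-sided 5%, and test one named SF-12 score at 6 months, also at two-sided 5%, only if the CDS is significant. The SF-12 may be labelled second primary or key secondary; the order is what matters. The Primary Aim and the hypothesis can go on naming both outcomes.

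The cost is wording. The sample size and the CDS power do not change. The drawback is that the SF-12 cannot support a primary claim when the CDS result is null.

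If the sponsor prefers two equal primaries, the article should state whether one or both must succeed and restate alpha and power to match. With either sufficient and 0.025 each, CDS power at 50 per group is about 72%, or 60 per group (150 enrolled) restores 80%. With both required, alpha stays at 5%, but the sponsor needs an SF-12 effect size and SD and should report the joint power.

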#### Cost-Effectiveness Analyses

A cost-effectiveness analysis (CEA) of the costs and outcomes for patients in the intervention and control groups will be undertaken. Detailed data on costs of Health Care Utilisation (HCU), access to community and other resources and medication are being collected from both the intervention and 'usual care' control groups. All resources utilised are costed using nationally applicable cost data (e.g. Diagnostic Related Groups costs for hospital admissions). Total medication costs are taken from patient contributions and estimated total Pharmaceutical Benefits Scheme benefits paid by the Health Insurance Commission. For HCU, data linkage with Medicare Australia's database allows the collection of health care utilisation data for use of items under Medicare and Pharmaceutical Benefits Scheme (PBS). Participants are requested to record current medications and number of general practitioner visits prior to Time 3 and Time 4 follow-up assessments.

The expected cost of readmission for ACS is also calculated using hospital-based costs and patient-specific probabilities of readmission for ACS computed using APACHE III (Acute Physiology And Chronic Health Evaluation III). The primary health outcome for the CEA is quality-adjusted life years (QALYs). These are calculated for both arms using HRQOL scores collected in the trial using the SF-6D, a derivative of the SF-12. The SF-12 instrument is widely used internationally, and has been recommended as appropriate and sensitive to change for CHD patients and in depression treatment [42]. For all economic analyses, detailed probabilistic sensitivity analysis will be undertaken for all projections and parameters with uncertainty and/or variability.

#### Intervention Implementation and Acceptability

To assess program implementation, participant acceptability is measured by a self-administered questionnaire at Time 2. Self-administered satisfaction questions include: 'how would you rate the MoodCare Participant Handbook' (*excellent *to *poor*); 'how would you rate your sessions with the Counsellor (*very useful *to *not useful at all)*; 'did you get what you expected from the program' (*yes definitely *to *no definitely not)*; 'to what extent has the program met your needs' (*almost all of my needs have been met *to *none of my needs have been met); *'has the program helped you to deal more effectively with your health issues' (*yes it helped a great deal *to *no it seemed to make things worse)*; 'in general how satisfied are you with the program (*very satisfied *to *very dissatisfied)*; 'were you satisfied with the length of the counselling sessions' (*yes, no)*; 'were you satisfied with the number of counselling sessions' (*yes, no)*; and 'were you satisfied with the length of the program overall' (*yes, no)*. Participants are also asked to highlight the strengths and weaknesses of the program in two open-ended questions. Participant adherence to the intervention is assessed by: the proportion of sessions completed during the intervention period; the topics covered in each session; and the total length (minutes) of intervention exposure during the six month period.

#### Long term maintenance and sustainability

The RE-AIM framework has been developed to evaluate the strengths and weaknesses of different approaches to chronic disease management [43]. This framework will be applied to further assess the feasibility of the MoodCare program. For example, we will evaluate the *Reach*, or representativeness of the sample by assessing the characteristics of eligible, enrolled and randomised participants. Similarly, to assess *Adoption*, characteristics on program uptake and adherence will be provided. The long term *Maintenance *of the program will be assessed by evaluating participant outcomes beyond six month follow up (e.g. 12, 24 months).

### Data Analyses

Baseline characteristics will be compared across intervention arms using summary statistics. Principal analyses will involve comparison of CDS and HRQOL outcomes at each time point between intervention arms using the baseline of the outcome as a covariate where relevant. Pooled analyses across all time points will employ linear mixed models. This will assess comparative rates of change over time, variability between rates of individuals, and allows for incomplete data due to a process of missingness where systematic dependence is upon observed covariates or outcomes, the so called "missing at random" assumption. Results will be expressed as estimated mean changes in CDS depression measures and HRQOL, as an overall mean excess intervention over usual care effect, all with corresponding 95% confidence intervals.

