**Methods:**

Over 1600 patients admitted after index admission for Acute Coronary Syndrome (ACS) are being screened for depression at six metropolitan hospitals in the Australian states of Victoria and Queensland. Consenting participants are then contacted at two weeks post-discharge for baseline assessment. One hundred eligible participants are to be randomised to an intervention or a usual medical care control group (50 per group). The intervention consists of up to 10 × 30-40 minute structured telephone sessions, delivered by registered psychologists, commencing within two weeks of baseline screening. The intervention focuses on depression management, lifestyle factors (physical activity, healthy eating, smoking cessation, alcohol intake), medication adherence and managing co-morbidities. Data collection occurs at baseline (Time 1), 6 months (post-intervention) (Time 2), 12 months (Time 3) and 24 months follow-up for longer term effects (Time 4). We are comparing depression (Cardiac Depression Scale [CDS]) and HRQOL (Short Form-12 [SF-12]) scores between treatment and UC groups, assessing the feasibility of the program through patient acceptability and exploring long term maintenance effects. A cost-effectiveness analysis of the costs and outcomes for patients in the intervention and control groups is being conducted from the perspective of health care costs to the government.

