#### Secondary Aims

(i) To investigate the longer term feasibility of implementing the MoodCare program at 12 and 24 months follow-up.

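### The Data Analyses section gives principal status to every follow-up time point and reports an overall mean effect, although six months is the declared primary assessment point and the basis of the sample size

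*Protocol article*

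**What the plan says.** Most of the protocol article points to six months. The section on changes in key depression and HRQOL outcomes states: "Six month follow up will be the primary assessment point". The closing hypothesis of the Background is also set at 6 months. Sample Size Calculations bases the 50 completers per group on a CDS difference of 6.8 at 6 months. The later follow-ups appear under Secondary Aims: "To investigate the longer term feasibility of implementing the MoodCare program at 12 and 24 months follow-up".

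Data Analyses ranks the time points differently. It says "Principal analyses will involve comparison of CDS and HRQOL outcomes at each time point between intervention arms", using the baseline value as a covariate where relevant, and does not single out 6 months. The post-baseline time points are 6, 12 and 24 months. The section then adds "Pooled analyses across all time points will employ linear mixed models" and says that results will be given as estimated mean changes and "as an overall mean excess intervention over usual care effect, all with corresponding 95% confidence intervals".

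Sample Size Calculations also gives a pooled analysis its own power statement, over a different window: "a pooled analysis at 6 and 12 months will have 80% power to detect a difference of 5.1 units". There are two primary outcomes: "The two primary outcomes are changes in depression and HRQOL which are assessed using the CDS [35] and SF-12 [36], respectively".

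**The concern.** The section that defines the analysis gives principal standing to comparisons that the aims treat as secondary, and the summary effect it describes answers a different question from the one the trial was sized on. The stated two-tailed 5% error for CDS holds if the 6-month contrast alone decides. Read literally, Data Analyses would let a 12- or 24-month difference be presented as a principal CDS result when the 6-month difference is null.

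The overall mean effect averages over follow-up that continues for 18 months after the six-month intervention period. Depending on how the effect evolves, it can disagree with the 6-month result. A later analysis plan cannot follow both sections: if it follows Data Analyses it departs from the declared primary assessment point, and the reverse.

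**Working it through.** **Inputs from Sample Size Calculations.** 50 completers per group, SD 12, difference 6.8 at 6 months, two-sided 5%, 80% power; correlation 0.30 between baseline, 6 and 12 months; pooled 6/12-month difference 5.1. Using 0.30 for 24 months as well is my assumption.

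**1. The plan's own figures.**
- 6 months, unadjusted: a two-sample t-test with 50 per group, difference 6.8 and SD 12 has 80.1% power and needs 49.9 per group for 80%. This reproduces.
- Pooled 6 and 12 months, baseline-adjusted: variance factor (1 + 0.30)/2 − 0.30² = 0.56. SE = 12 × √0.56 × √(2/50) = 1.796. The detectable difference is (1.960 + 0.842) × 1.796 = 5.03, and power at 5.1 is 81.0% (normal approximation). This agrees with the stated 5.1.

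Each figure is for one CDS contrast tested alone at 5%.

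**2. Correlation between the time-point statistics.** After baseline adjustment: (0.30 − 0.30²)/(1 − 0.30²) = 0.21/0.91 = 0.231. I also used 0.5 and 0.7 as assumed higher values.

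**3. Chance of at least one false positive for CDS if any listed contrast could be claimed.** Simulated null z-statistics for 6, 12 and 24 months, each tested at |z| > 1.96; the pooled z is their standardised sum.

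| Correlation between statistics | 6, 12 or 24 months | plus pooled effect | 6 months or pooled only |
|---|---|---|---|
| 0.231 | 13.9% | 14.9% | 8.4% |
| 0.5 | 12.5% | 12.9% | 7.7% |
| 0.7 | 10.9% | 11.1% | 7.1% |

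For reference, three independent tests give 1 − 0.95³ = 14.3%. If the 6-month contrast alone decides, the rate is 5%.

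**4. Six-month effect against overall effect.** Baseline-adjusted SE at 6 months: 12 × √0.91 × √(2/50) = 2.289. The mean of three time points has variance factor (1 + 2 × 0.231)/3 = 0.487 relative to one, so SE = 2.289 × √0.487 = 1.598. Power is Φ(effect/SE − 1.96). At 6 months, 6.8/2.289 = 2.97, so power is 84%. The effect patterns below are assumed.

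| CDS difference at 6 / 12 / 24 months | Mean | Mean/SE | Pooled power | Verdicts differ |
|---|---|---|---|---|
| 6.8 / 3.4 / 0 | 3.40 | 2.13 | 57% | 32% |
| 6.8 / 5.0 / 3.4 | 5.07 | 3.17 | 89% | 14% |
| 6.8 / 6.8 / 6.8 | 6.80 | 4.26 | 99% | 15% |

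The last column is the simulated share of trials in which one test is significant and the other is not. The pooled effect has less power than the 6-month test under steep fading and more under mild fading or persistence.

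**The case against.** The strongest reply is that the ranking is already stated: the hypothesis, the sample size and the outcomes section all point to 6 months, and the later visits fall under a secondary aim. On that view, Data Analyses describes how comparisons are made, and principal may mean only the main modelling approach. A reader can reasonably infer that the 6-month contrast decides. That softens the point, but the wording still attaches principal status to every time point and remains to be reconciled.

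A reader might go further and infer that four CDS contrasts, each at full alpha, decide the trial, so that its error rate is about 15%. The documents do not support this. Nowhere do they say that any one significant contrast is enough. The pooled analysis stands in its own sentence and is not called principal. The section promises estimates with 95% confidence intervals and sets out no testing rule. The rates above are therefore conditional.

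A reader might also infer that the overall effect necessarily hides a real 6-month benefit. It does so only if the effect fades steeply. The sample-size section assumes persistence to 12 months, the mixed model is meant to assess rates of change over time, and the results sentence also mentions estimated mean changes, so the 6-month result is not necessarily displaced.

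Two further replies have some force. The lack of a gatekeeping scheme or alpha split is not a fault in a condensed article and is not counted here. The feasibility label lowers the stakes, although the trial is powered on CDS and the Discussion speaks of evaluating efficacy.

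**Conclusion.** The point holds as an internal inconsistency. Six months is primary by declaration, hypothesis and sizing, yet Data Analyses makes each time point principal and expresses results as an overall mean effect that differs from the contrast the trial was sized on.

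Its possible size for CDS is a false-positive chance of about 11% to 14% instead of 5% if any of the three time points could be claimed, and about 11% to 15% with the pooled effect included. These figures rest on an any-contrast rule that the wording allows but the protocol does not state, on correlations between statistics of 0.7 down to 0.23, and on extending the correlation of 0.30 to 24 months. No general statement that the pooled effect is weaker or stronger is justified. The change is worth making because it costs almost nothing and secures the 5% error on which the sample size rests.

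**What to change.** In Data Analyses, state that the principal comparison for each primary outcome (CDS, on which the trial is sized, and SF-12) is the between-arm difference at 6 months adjusted for the baseline value of that outcome, and that this difference is reported as the main result. Label the 12-month and 24-month comparisons and the pooled or overall mixed-model estimates as secondary, reported with 95% confidence intervals. Give the pooling window consistently, since Sample Size Calculations uses 6 and 12 months and Data Analyses uses all time points. The wording should keep SF-12 as a primary outcome.

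The cost is an edit to the text, with no extra participants or data; 50 completers per group still gives 80% power for 6.8 at 6 months. The downside is that a benefit seen only at 12 or 24 months, or only in the pooled estimate, could not be claimed as a principal result.
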